## Participants

3

This will be a multi‐center study enrolling adult patients (≥ 18 years old), regardless of sex, from 20 Basic Health care Units (BHUs) from the Federal District (DF, Brazil). Participants will be randomly selected from the pool of registered diabetic individuals meeting trial eligibility.

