## Interventions

5

Participants in the control arm will receive treatment at the discretion of their physician, without interference from the study personnel, and they will be followed up through app interactions, phone calls, and lab exams every 24 weeks.

Both study arms are recruited and followed within the same BHU of the Brazilian Primary Health Care Network, ensuring comparable clinical settings and multidisciplinary staff. Usual care in these units is provided by PCPs and nurses and is defined as routine management typically involving in‐person consultations every 3–6 months according to clinical need, with medication adjustments and laboratory testing performed at the physician's discretion, and no structured digital follow‐up. In the control arm, no standardized algorithms or automated decision‐support tools are used, and there are no scheduled tele‐touchpoints beyond those required for data collection. All usual‐care contacts and visit frequencies will be documented to allow comparison of exposure intensity between study arms. To minimize contamination between study arms, the structured remote workflow is delivered exclusively by the trained study monitors assigned to the intervention arm. Control participants do not have access to TAMIS‐IA clinical decision support, automated titration protocols, or structured telemonitoring beyond protocol‐required data collection. Usual care providers remain independent from the intervention workflow, and no algorithm‐driven recommendations are integrated into routine care.

Participants in the active intervention arm will receive treatment based on standardized clinical guidelines, with instructions provided remotely by study monitors under physician supervision. The study monitors are health care professionals and research fellows with clinical backgrounds, specifically trained to conduct structured telephone follow‐ups, data collection, and patient education activities. The intervention is supported by TAMIS‐IA, a web‐based digital health platform that enables remote management, patient monitoring, and clinical decision support. All medication adjustments or new prescriptions generated through the digital platform are reviewed and formally approved by physicians before implementation to ensure clinical safety and protocol compliance. Further technical and operational details of the platform are provided in Supporting Information S1: Material 2.

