## Sample Size Calculation

7

Given that a comprehensive multifactorial intervention targeting intensive cardiovascular risk factor control has been associated with significant reductions in cardiovascular mortality (−57%), cardiovascular events (−59%), and hospitalizations due to heart failure (HF) in patients with diabetes [1], this study was designed using a standard win ratio test. The win ratio test incorporates both all‐cause mortality and all‐cause hospitalizations, using component‐wise hazard ratios (HRs) as effect size estimators.

For the sample size estimation, predefined hazard ratios (HR 0.90 for all‐cause death and HR 0.70 for all‐cause hospitalization) were used, targeting 90% statistical power with a two‐sided *α* = 0.05% and 5% expected attrition. Sensitivity analyses explored plausible variations in baseline event rates and component HRs to confirm robustness of the win‐ratio and power assumptions. A total of 838 participants (419 per treatment arm) will provide adequate power under these scenarios. Sample size calculations were performed in R (v1.2) using the WR package, as described by Mao et al. and Yu et al. [14, 15]. Supporting Information Material 4 summarizes the simulation scenarios and corresponding sample size estimates.

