### Type of Randomization

9.2

A stratified randomization approach will be employed to ensure balance between the study arms. Stratification will be based on key demographic and clinical characteristics, including age (< 55 or ≥ 55 years), gender and prior cardiovascular disease. Within each stratum, randomization will follow a permuted block design with block sizes randomly varying between four and eight, ensuring equal representation of each intervention arm within each stratum.

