For non–time‐to‐event secondary endpoints, including changes in metabolic and clinical parameters (blood pressure, HbA1c, LDL‐C) and patient‐reported outcomes, analyses will be performed using paired t‐tests and analysis of covariance (ANCOVA) models, incorporating baseline values as covariates. Treatment differences will be evaluated at a two‐sided alpha level of 0.05, applying the same hierarchical procedure used for time‐to‐event endpoints to control type I error. All analyses will follow the ITT principle, and sensitivity analyses will be conducted to assess the impact of missing data.

For the tertiary endpoint analysis, the study will evaluate changes in the MeTaRiSc from baseline to Week 84. Each participant will receive a score of 1 for each parameter above the target; the total score will then be divided by three, producing a weighted mean ranging from 0 to 1. A paired t‐test will compare the two treatment groups. Treatment differences will be tested at an alpha level of 0.025, using a sequential type 1 error correction procedure. Covariate adjustments will be made using a *t*‐test, incorporating the randomization stratification factor. The mean values for each treatment group (intervention vs. control) will be reported with the corresponding 95% CI.

All subgroup analyses will involve log‐rank tests and the hazard ratios (with 95% CIs) for primary and secondary efficacy endpoints. The predefined subgroups include sex, age (< 65 vs. ≥ 65 years), prior cardiovascular disease, presence of cardiovascular risk factors (diabetes, hypertension, chronic kidney disease), smoking history (active vs. significant past smoking), obesity/metabolic syndrome, and prior statin use.

The present study was designed in accordance with the NIH‐FDA Clinical Trial Protocol Template. A structured protocol and a Statistical Analysis Plan (SAP) were developed prior to participant enrollment, specifying the analytic approach for all predefined endpoints, including sensitivity and subgroup analyses.

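### The stated ANCOVA and Cox models leave out BHU, a modest loss of precision, and no sensitivity analysis covers possible clustering by study monitor in the intervention arm

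*Protocol article*

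**What the plan says.** - **Setting.** Section 3 (Participants) draws the sample "from 20 Basic Health care Units (BHUs) from the Federal District (DF, Brazil". Section 5 (Interventions) adds: "Both study arms are recruited and followed within the same BHU of the Brazilian Primary Health Care Network, ensuring comparable clinical settings and multidisciplinary staff".
- **Allocation.** Section 9.2 randomizes individuals in permuted blocks within strata, "including age (< 55 or ≥ 55 years), gender and prior cardiovascular disease". BHU is not named.
- **Models.** Section 9.4 analyses continuous secondary outcomes with paired t-tests and "analysis of covariance (ANCOVA) models, incorporating baseline values as covariates". Its Cox models carry the randomization stratification factor. Neither has a term for BHU or for study monitor.
- **Delivery.** Section 5 says the remote workflow is "delivered exclusively by the trained study monitors assigned to the intervention arm". Sections 5.1 to 5.3 describe what the study team does by telephone: counseling, medication adjustment and follow-up every 4–6 weeks.
- **Safeguards.** Section 5 also describes standardized training, verified competency and physician approval of prescriptions. Section 5.2 says titration follows an algorithm in the software.
- **Analyst blinding.** Sections 8 and 9.3 conceal allocation from the analysts after data lock.

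**The concern.** Two separate matters arise.

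**BHU.** Local care and admission practice can differ between 20 units. The unit is known for every participant and cuts across both arms, so it is a natural adjustment variable. Leaving it out keeps between-unit variation in the residual. It also leaves any chance imbalance of arms within units uncorrected in the estimate.

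**Monitors.** In the intervention arm, participants may share a monitor, and so share that person's counseling and follow-up style. Controls have no such grouping. Correlation of this kind arises after allocation, so randomization does not remove it. An analysis that treats all participants as independent would then report intervals that are too narrow. The exposed outcomes are those closest to the monitors' work: HbA1c, LDL-C, blood pressure and quality of life.

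**Working it through.** **Inputs from the protocol article.** Section 7: "A total of 838 participants (419 per treatment arm) will provide adequate power under these scenarios", with 5% attrition. Section 3: 20 BHUs. Evaluable participants: 838 × 0.95 = 796, or 398 per arm. Participants per BHU: 838 / 20 ≈ 42. The article gives no figure of its own for BHU or monitor effects. The 838 itself cannot be re-derived here because the baseline event rates stand in a supplement that is not shown; nothing below depends on it beyond the counts.

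**Assumed inputs (not in the document).** Share of outcome variance due to BHU: 0.02–0.10. Number of monitors J: 5–40. Monitor intraclass correlation (ICC): 0.005–0.05. Each participant is served by one monitor.

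**1. BHU: validity.** Allocation is individual and independent of BHU, so between-unit variance is already contained in the unadjusted standard error. Simulating 838 participants in 20 BHUs with an unadjusted t-test gave type I error between 4.7% and 5.2% for BHU shares of 0.02–0.10. There is no inflation.

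**2. BHU: precision (continuous outcomes).** Variance without BHU relative to variance with it = 1 / (1 − share).

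| BHU share | Variance ratio | Excess variance |
|---|---|---|
| 0.02 | 1 / 0.98 = 1.020 | 2.0% |
| 0.05 | 1 / 0.95 = 1.053 | 5.3% |
| 0.10 | 1 / 0.90 = 1.111 | 11.1% |

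For a continuous outcome with 90% power unadjusted, adjustment would give 90.6%, 91.4% and 92.7%.

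**3. BHU: chance imbalance.** Simulated allocation as planned (8 strata, blocks of 4, 6 or 8, 20 equal BHUs) gives a standard deviation of the within-BHU arm difference of about 6 participants. About 3 of 20 BHUs split 60:40 or worse, and there is roughly an even chance that at least one splits 2:1 or worse.

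**4. Monitors: one-arm clustering.** Design effect in the intervention arm: DE = 1 + (398/J − 1) × ICC. Variance ratio of the treatment contrast: V = (DE + 1) / 2. Actual error of a nominal 5% test: 2 × [1 − Φ(1.96 / √V)].

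| J | ICC | DE | V | True SE / reported SE | Actual error |
|---|---|---|---|---|---|
| 40 | 0.005 | 1.045 | 1.022 | 1.01 | 5.3% |
| 20 | 0.01 | 1.189 | 1.095 | 1.05 | 6.1% |
| 10 | 0.01 | 1.388 | 1.194 | 1.09 | 7.3% |
| 10 | 0.02 | 1.776 | 1.388 | 1.18 | 9.6% |
| 10 | 0.05 | 2.940 | 1.970 | 1.40 | 16.3% |
| 5 | 0.05 | 4.930 | 2.965 | 1.72 | 25.5% |

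With all 419 per arm instead of 398, the last row becomes 26.3%. If several monitors share a participant, all these figures shrink.

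**5. Why not stratify allocation by BHU.** The present 8 strata × 20 BHUs = 160 cells, and 838 / 160 ≈ 5 participants per cell. Blocks of 4 to 8 would often not fill.

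**The case against.** The strongest reply is that this is detail for the SAP, which section 9.4 says was written before enrollment and which is not shown. The word introducing the strata in section 9.2 can also be read as non-exhaustive. That lowers the weight of the point but does not remove it. The article names the models and their covariates, so adding BHU changes a stated method.

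Four stronger readings are tempting, and the documents do not support them:

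- **That the sentence on shared BHUs is wrong.** It claims comparable settings and staff, not equal numbers per unit. Individual randomization within shared units supports it, so it needs no rewording.
- **That omitting BHU biases the result or invalidates the test.** Step 1 shows that it does not. The gain from adjustment is efficiency alone.
- **That the planned standard errors are too small because of monitors.** Section 5 assigns monitors to the arm; nothing says that each participant has a fixed monitor. Their number, caseload and ICC are not given. Software algorithms, physician approval and standardized training point to a low ICC, and 26% is the extreme corner of an assumed range.
- **That the primary result is undermined.** Death and hospitalization are less exposed to monitor differences than the risk-factor outcomes. The 1 / (1 − share) formula belongs to linear models and should not be turned into participants lost from a sample size built for a win ratio.

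**Conclusion.** The point holds in a limited form. Leaving BHU out of the stated ANCOVA and Cox models costs about 2–11% of variance for continuous outcomes if BHU explains 2–10% of outcome variance, which is an assumption. The comparison stays unbiased and type I error stays at about 5%.

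The monitor matter is conditional: it arises only if participants are served by particular monitors and monitors differ. Over 5–40 monitors and ICC 0.005–0.05 (both assumed), true error runs from about 5% to 26%, and the described standardization makes the low end more plausible. That justifies a sensitivity analysis of the secondary outcomes, not a change to the main analysis.

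**What to change.** **In section 9.4, main analyses.** Add BHU as a random intercept or fixed effect to the ANCOVA models. Stratify the Cox models by BHU, or use a BHU frailty. Do both alongside the randomization factors. Leave the randomization strata, the Interventions wording and the win-ratio test as they are. Participants are recruited by BHU, so the cost is a few lines of text.

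**In section 9.4, sensitivity analysis.** For HbA1c, LDL-C, blood pressure and quality of life, pre-specify a partially nested model: a random monitor effect in the intervention arm only, with a small-sample correction because a variance estimated from few monitors is imprecise. Two conditions apply:

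- Confirm first that the platform links each participant to a monitor. The audit trail in section 5 covers user access, data entry and edits, which may not be the same thing.
- Run it after the blinded main analysis. A monitor identifier present in only one arm would reveal allocation, contrary to sections 8 and 9.3.

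The downside is somewhat wider intervals in that sensitivity analysis if monitors do differ.

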### Lifestyle Management

5.1

At the beginning of the study, trained study monitors will interview patients to assess their health habits and provide individualized counseling on lifestyle modifications. The educational approach will emphasize weight loss, physical activity, and the reduction of sodium and alcohol consumption. Patients will have continuous access to navigators, who can answer questions and address concerns. During every follow‐up call, lifestyle modifications will be reviewed, with specific counseling on smoking cessation, including access to resources for quitting. Additionally, medication adherence will be reinforced through the recommendation of once‐daily drug regimens and combination therapies. Each call will also include a review of individual treatment goals.

### Blood Pressure Management

5.2

A SAH treatment algorithm was developed based on the 2025 Brazilian Hypertension Guideline [11]. Figure 3 illustrates the clinical workflow for SAH management, including the initiation and titration of pharmacological treatment. Upon enrollment, patients will measure their BP at home for six consecutive days, following a standardized protocol: twice in the morning and twice in the evening, always before taking antihypertensive medications. Patients will receive home BP monitors, equipped with technology that enables real‐time transmission of BP readings to the EHR via Bluetooth.

**Figure 3 jep70456-fig-0003:**
[figure not shown]
Hypertension management algorithm: treatment initiation, titration, and referral pathways. ACEi, angiotensin‐converting enzyme inhibitor; ARB, angiotensin receptor blocker; BP, blood pressure; CCB, calcium channel blocker; CKD, chronic kidney disease; DM, diabetes mellitus; HBPM, home blood pressure monitoring; HCTZ, hydrochlorothiazide.

A customized software platform was developed to automatically calculate weekly BP averages, defining target BP as a weekly systolic BP (SBP) < 130 mmHg and diastolic BP (DBP) < 80 mmHg. The system allows for dynamic adjustments of BP targets based on individual clinical indications.

For patients whose home BP remains elevated, medication adjustments will be conducted remotely, via telephone consultations with a patient monitor, following the clinical algorithm integrated into the software platform. Physicians will review and approve all new prescriptions before implementation. This approach allows for more frequent medication titrations than in standard clinical practice.

After each titration, patients will wait 1 week for stabilization before repeating another 6‐day BP measurement cycle at home. This results in a biweekly cycle of medication titrations, which aligns with the pharmacokinetics of the prescribed antihypertensive agents, including angiotensin‐converting enzyme (ACE) inhibitors, angiotensin‐receptor blockers (ARBs), calcium channel blockers (CCBs), and diuretics.

This accelerated titration protocol aims to overcome the therapeutic inertia commonly seen in traditional BP management. Throughout the study, electrolytes and renal function will be monitored when clinically indicated. Once patients achieve BP control, they will transition out of the intensive titration phase, moving to a surveillance phase with follow‐ups every 6 months.

If a participant's home BP remains elevated despite the use of three antihypertensive agents, including a diuretic, they will be classified as having resistant hypertension and automatically referred to a SAH specialist for further evaluation and treatment.

### Glucose Management

5.3

A pharmacologic treatment algorithm for hyperglycemia and diabetes was developed based on the ADA guidelines [12]. Figure 4 illustrates the clinical workflow for diabetes management, detailing the stratification of patients according to cardiovascular risk, comorbidities, and therapeutic goals. First‐line therapy will primarily involve metformin, unless other compelling indications warrant a different approach. The choice of therapy will be patient‐centered, taking into account clinical history, comorbidities, and individual preferences.

**Figure 4 jep70456-fig-0004:**
[figure not shown]
Diabetes management algorithm: stratification, treatment, and monitoring strategies. *If eGFR is adequate. ^Empagliflozin and dapagliflozin have shown benefits in dedicated HF trials. Canagliflozin demonstrated a reduction in HF hospitalization in cardiovascular outcome trials. #Dapagliflozin and canagliflozin showed benefits in kidney outcome studies. Empagliflozin demonstrated a reduction in CKD progression in cardiovascular outcome studies. + Weight loss is greater with semaglutide > liraglutide > dulaglutide > exenatide > lixisenatide. ASCVD, atherosclerotic cardiovascular disease; CKD, chronic kidney disease; DPP‐4i, dipeptidyl peptidase‐4 inhibitor; eGFR, estimated glomerular filtration rate; GLP‐1 RA, glucagon‐like peptide‐1 receptor agonist; HF, heart failure; HFrEF, HF with reduced ejection fraction; SFU, sulfonylurea; SGLT2i, sodium‐glucose cotransporter‐2 inhibitor; TZD, thiazolidinedione.

Patients diagnosed with diabetes will be monitored every 4−6 weeks by the study team to assess their adherence to lifestyle modifications and pharmacological treatment. Laboratory tests, including HbA1c, fasting glucose, and capillary blood glucose (or continuous glucose monitoring data), will be reviewed every 12 weeks. During the scheduled visit week in which laboratory testing is planned, participants will be instructed to undergo blood sample collection at the designated research laboratory affiliated with the study. Laboratory results are securely shared with patients and monitors, and trained staff record verified values in the study database. Additionally, study monitors will recommend visits to the PCP every 12–24 weeks to screen for signs of neuropathy or polyneuropathy.

All prescriptions will follow a structured protocol, supervised by experienced physicians. Medication doses will be adjusted as needed to ensure patients achieve their glycemic targets, such as HbA1c levels, considering their cardiovascular and renal status. Therapy adjustments will also account for the risk of hypoglycemia, cost‐effectiveness, and patient preferences.

### LDL‐C Management

5.4

A treatment algorithm for LDL‐C management was developed based on the 2025 Brazilian Guideline on Dyslipidemias and Atherosclerosis Prevention [13]. Figure 5 outlines the clinical workflow for managing LDL‐C, including medication selection, dosing adjustments, and monitoring strategies. The treatment recommendations will include specific regimens for statins, ezetimibe, and strategies for managing statin intolerance. Medication selection and dosing will be tailored according to patient history, considering factors such as concomitant medications, prior ASCVD events, previous lipid‐lowering therapies, and laboratory data, including creatine kinase (CK), estimated glomerular filtration rate (eGFR), alanine aminotransferase (ALT), and aspartate aminotransferase (AST).

**Figure 5 jep70456-fig-0005:**
[figure not shown]
Algorithm for LDL‐C management: medication selection, dosing, and monitoring. *Intermediate Risk (Target LDL‐C: < 100 mg/dL): Initiate simvastatin 40 mg/day and titrate the dose based on LDL‐C levels. If necessary, consider adding ezetimibe 10 mg/day or increasing to atorvastatin 20 mg or rosuvastatin 10 mg. **High Risk (Target LDL‐C: < 70 mg/dL) or Very High Risk (Target LDL‐C: < 50 mg/dL): Initiate atorvastatin 40−80 mg/day or rosuvastatin 20−40 mg/day. CPK, creatine phosphokinase; GFR: Glomerular Filtration Rate; LDL‐C, Low‐Density Lipoprotein Cholesterol.

Before entering the LDL‐C management program, a manual verification of contraindications to lipid‐lowering therapy will be required. Relative contraindications include ALT or AST ≥ 5 times the upper limit of normal, CK ≥ 10 times the upper limit of normal, eGFR ≤ 30 mL/min/1.73 m^2^, or documented allergies to lipid‐lowering therapy. Absolute contraindications include pregnancy, pre‐conception planning, breastfeeding, hemodialysis, New York Heart Association (NYHA) class II‐IV HF, or severe psychiatric conditions. Any cases with a relative or absolute contraindication will be discussed with the supervising pharmacist and/or cardiologist.

A clinical algorithm software application was developed to generate individualized therapeutic recommendations for lipid management and track each participant's progress. This system integrates demographic, laboratory, medication, and medical history data through an application programming interface (API) server, allowing for the automated generation of treatment recommendations and follow‐up laboratory testing schedules. Additionally, the software incorporates a scheduling tool for follow‐up calls, laboratory testing, documentation, and coordination of patient care management, ensuring compliance with Brazilian General Data Protection Laws (LGPD).

